## Abstract

**Background:**

Low back pain is a common disorder in western industrialised countries and the type of treatments for low back pain vary considerably.

**Methods:**

In a randomised controlled trial the cost-effectiveness and cost-utility of an intensive group training protocol versus physiotherapy guideline care for sub-acute and chronic low back pain patients is evaluated. Patients with back pain for longer than 6 weeks who are referred to physiotherapy care by their general practitioner or medical specialist are included in the study. The intensive group training protocol combines exercise therapy with principles of behavioural therapy ("graded activity") and back school. This training protocol is compared to physiotherapy care according to the recently published Low Back Pain Guidelines of the Royal Dutch College for Physiotherapy. Primary outcome measures are general improvement, pain intensity, functional status, work absenteeism and quality of life. The direct and indirect costs will be assessed using cost diaries. Patients will complete questionnaires at baseline and 6, 13, 26 and 52 weeks after randomisation.

**Discussion:**

No trials are yet available that have evaluated the effect of an intensive group training protocol including behavioural principles and back school in a primary physiotherapy care setting and no data on cost-effectiveness and cost-utility are available.

## Background

Low back pain is a very common complaint with major social and economical consequences. In a recent cross-sectional study the annual prevalence of low back pain in the general Dutch population was estimated at 44% [1]. The course of low back pain is usually relatively short: about 80–90% of people with low back pain spontaneously recover within four to six weeks. However, approximately 1–7% develop chronic low back pain. Although this is a relatively small group, the economic consequences are enormous [2]. The total costs of low back pain in the Netherlands in 1991 have been estimated at 1.7% of the Gross National Product [3]. About 93% of the total costs were due to absenteeism and disablement. Because of the enormous costs related to low back pain, effective interventions aimed at prevention and treatment of chronic complaints are necessary. The Cochrane Collaboration has published several systematic reviews on the effectiveness of different treatments for low back pain. Exercise therapy, back schools and behavioural therapy seem to be the most promising interventions for treatment of chronic low back pain [4]. Authors recommended future trials with sufficiently large sample sizes and sufficiently long follow-up periods. Cost-effectiveness and cost-utility analyses of treatments were also recommended, because the observed differences in effectiveness were only small.

Evidence-based physiotherapy for sub-acute and chronic low back pain patients consists of adequate information and an active approach, including behavioural principles. As physiotherapists have not yet put these principles into practice [5-7] two important barriers have to be dealt with. First, changing behaviour of health care providers is always very difficult, even when guidelines are actively implemented [8]. Second, physiotherapists usually do not have specific knowledge of behavioural principles and are usually not specifically trained to provide behavioural therapy. To solve these issues, physiotherapists in Amsterdam have developed a new intervention program. This program not only makes optimal use of the combination of the principles of exercise therapy, behavioural therapy and back schools, but has structured it into a protocol that facilitates physiotherapists to perform this intervention in clinical practice. This trial will evaluate the cost-effectiveness and cost-utility of the intensive group training protocol compared with physiotherapy guideline care.

## Methods

### Study design

The study is a randomised controlled trial (RCT). Alongside the trial a full economic evaluation will be conducted. The Medical Ethics Committee of VU University Medical Centre has approved the study design, protocols and informed consent procedures.

### Setting

The trial will be conducted in a primary physiotherapy care setting in Amsterdam and its surroundings. Eighty-five physiotherapists will participate in the trial; 40 physiotherapists are trained to provide the intensive group training protocol and 45 physiotherapist are instructed to provide usual physiotherapy care according to the Low Back Pain Guidelines of the Royal Dutch College for Physiotherapy (KNGF).

### Study population

Patients with non-specific low back pain referred to one of the participating physiotherapists by their general practitioner are eligible for participation in the trial. Patients are included if the current episode of low back pain lasts more than 6 weeks and if the complaints show no tendency to decrease, meaning that the patient has not increased his activities in the last three weeks. Furthermore, patients have to be between the age of 18 and 65 years old, live or work in Amsterdam and have a health insurance with one insurance company (Agis). This health insurance company covers about 80 to 90 percent of the Amsterdam population and is the only company that reimburses the intensive group training protocol. Patients are excluded from the study if 1) they have specific low back pain, attributable to e.g. infection, tumour, osteoporosis, rheumatoid arthritis, fracture, inflammatory process, radicular syndrome or cauda equina syndrome; 2) their general practitioner or medical specialist advised them not to perform physically straining activities; 3) they are pregnant; 4) they have pelvic pain/instability; 5) they are dealing with a lawsuit related to either their low back pain or related to their disability for work. Patients are recruited by participating physiotherapists. If patients are interested in participating in the trial, they receive written information about the trial and their name and phone number is given to a research assistant. The research assistant calls the patient two days later and explains the aim and implications of the study. If the patient agrees to participate, an appointment is made at a local research centre. At the local research centre a research physiotherapist checks again if the patients meets the eligibility criteria. Patients who meet the criteria and agree to participate in the trial must sign an informed consent form. Patients are asked to complete baseline questionnaires and the research physiotherapist will conduct baseline assessment of physiologic outcome measures.

In accordance with the CONSORT statement, information on number of recruited and eligible patients and reasons for exclusions or refusal to participate will be registered for all recruited patients by the participating physiotherapists and the research physiotherapist.

### Treatment allocation

Patients are randomly assigned to either the intensive group training protocol or physiotherapy guideline care. Randomisation is stratified for duration of complaints to ensure a sufficient number of sub-acute and chronic patients in each treatment group. To avoid inconvenience for the patients, seven local research centres are set up in different parts of the city. For each research centre two randomisation lists are prepared and permuted blocks of 4 patients are made to ensure equal distribution of patients for each research centre. An independent statistician generated the randomisation lists, using series of random numbers. The principle investigator ([name]), who is not involved in the selection of patients, prepared the opaque, sealed envelopes, guaranteeing concealed randomisation. At the local research centre the administrative assistant hands the next envelope to the patient who then opens the envelope. The administrative assistant then checks the envelope and informs the participating physiotherapist about the treatment allocation.

### Blinding

Both the research physiotherapists and the principle investigator remain blinded for the allocation of treatment. Patients cannot be blinded for the interventions. As a consequence most outcome measures, consisting of self-report questionnaires are not blinded either. All physical outcome measures are blindly assessed by the research physiotherapist as we ask the patients not to reveal information about their treatment to the research physiotherapists. Participating physiotherapists can not be blinded for treatment allocation, but they are not involved in the assessment of outcome measurements.

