The exercises mentioned at point 4. are determined by a Patient Main Complaint Form [11]. During the first intake patients are given this form, consisting of thirty different activities (e.g. turning in bed, lifting, walking, etc.). The patient is asked to select and prioritise the activities he has had trouble with during the last week and would very much like to see improved in the following months. The physiotherapist discusses the form with the patient and designs specific exercises for these activities. Three baseline measurements are performed to determine the maximal performance (for example, the maximum number of repetitions) for each exercise separately. The starting point of the program is 70% of the mean of all three measurements, in order to avoid failure and ensure the experience of success. In agreement with the patient the training quota are determined by the physiotherapist using the starting point, goals and training period to provide a gradually increasing program. The exercise goals are determined by the patient and physiotherapist together to ensure that goals are realistic, concrete, trainable and measurable. The treatment contract is signed by the patient and physiotherapist. The contract states that training quota are always followed exactly and that the patient keeps the graphs of finished sessions.

For training, the physiotherapists will receive instruction on the background and content of the protocol, and will be trained to include behavioural principles in the physiotherapeutic management of low back pain at two meetings of six hours each. In groups of 7–8 physiotherapists discussions and role playing are supervised by one expert trainer with extensive experience in behavioural principles. Four months after the last meeting 2 follow up sessions of 4 hours are organised to discuss practical problems and practice difficult situations with the trainers. The principal investigator ([name]) will regularly visit the group sessions at the physical therapy practices to monitor the conduct of the intensive group training protocol. For each participating patient the physiotherapist is asked to complete a registration form containing the treatment goals, content of the different sessions and evaluation of the protocol.

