### Contrast physiotherapy guideline care and intensive group training protocol

The intensive group training protocol is a standardised approach consisting of 30 treatment sessions. As the physiotherapy guideline care is not a protocol, the number of sessions will vary per patient. In daily practice the average number of treatment sessions is 9 and the average duration of treatment is 6 weeks [6]. The organisation of the intensive group training protocol is based on back school principles and will take place in groups of 5–8 patients. The physiotherapy guideline care is organised as usual physiotherapy care and patients are treated individually. The guidelines recommend exercise therapy with a behavioural approach. However, no further guidance is provided regarding the content of the exercise program (type, intensity, frequency and duration of exercises) or regarding integrating behavioural principles. In the intensive group training protocol the content of the exercise therapy, back school and operant condition are thoroughly described and the physiotherapists are trained to apply these skills in practice. So the contrast lies in the number of sessions, group versus individual therapy and the conduct of the behavioural therapy.

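### The principal investigator is declared blinded to allocation but is to visit the group sessions, which only the intensive arm receives

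*Protocol article*

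**What the plan says.** The Blinding section of the protocol article makes an unqualified statement: "Both the research physiotherapists and the principle investigator remain blinded for the allocation of treatment". It adds that patients and treating physiotherapists cannot be blinded and that the self-report questionnaires, which are most of the outcome measures, are therefore unblinded. For the physical tests it says: "All physical outcome measures are blindly assessed by the research physiotherapist".

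Two other sections give the principal investigator tasks that bear on this.

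- **Interventions.** In the account of how the intensive-arm physiotherapists are trained and followed up, the principal investigator "will regularly visit the group sessions at the physical therapy practices to monitor the conduct of the intensive group training protocol".
- **Treatment allocation.** "An independent statistician generated the randomisation lists, using series of random numbers". The envelopes are then attributed to the principal investigator, "who is not involved in the selection of patients, prepared the opaque, sealed envelopes, guaranteeing concealed randomisation".

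The section contrasting the two treatments says how each is delivered. The intensive programme "will take place in groups of 5–8 patients". For the comparator: "The physiotherapy guideline care is organised as usual physiotherapy care and patients are treated individually".

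**The concern.** The mode of delivery identifies the arm. Someone who attends a group session knows that the trial patients in the room were allocated to the intensive programme, so a person who does this regularly cannot also remain blinded.

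What is at stake is the accuracy of a stated safeguard. Patients and therapists know the treatment, and all five primary outcomes are reported by the patient, so the article has few blinding protections to offer. It names two roles as blinded, and the statement fails for one of them. A reader would credit the trial with a lead investigator who does not know individual allocations, and might assume that decisions on data handling, costing or analysis were shielded accordingly. If the principal investigator takes part in such decisions, which the article neither says nor excludes, that shield would be missing for the patients seen.

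**Working it through.** There is no figure of the plan to reproduce. The check is whether the statements can all be true together.

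1. **Same role.** Names are removed from the text, so identity rests on the role title. It is the same under Treatment allocation, Blinding and Interventions, apart from the spelling principle/principal.
2. **What the visits show.** The visits are to group sessions of the intensive programme. Only that programme is delivered in groups. Presence at a session therefore reveals the arm, provided that the patient attends the treatment allocated and is recognisable as a trial participant.
3. **Is there a reconciling safeguard?** The article describes none: no other monitor, no restriction of visits to sessions without trial patients, and no limit of the blinding statement to a particular task or period. The statement and the visits cannot both stand for the patients seen.
4. **What the envelopes add.** Preparing allocation envelopes from the statistician's lists plausibly means seeing the sequence. It does not show which patient received which envelope. There are seven centres with two lists each, so 7 × 2 = 14 lists. Linking a list position to a person would need the order of enrolment within each list, and the article does not say that the principal investigator follows this. The envelopes are supporting evidence only.
5. **How many patients.** Planned recruitment is 280 (Sample size). With equal allocation, 280 / 2 = 140 are in the intensive arm. One visit to one group discloses 5 to 8 allocations if all members are trial patients. Under the same assumption the arm forms between 140 / 8 = 17.5, so about 18, and 140 / 5 = 28 groups, and one visit to each would disclose all 140, apart from absences. The article says only that visits are regular. The number disclosed therefore lies somewhere between one group and the whole arm.
6. **What the visits do not show.** They give no direct information on guideline-care patients, who are treated individually and are not visited.

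**The case against.** The strongest reply is that the contradiction has no demonstrated consequence. The article gives the principal investigator no part in outcome assessment. The primary outcomes come from patient questionnaires and do not pass through this person. No analyst is named and blinded analysis is not claimed; coded-arm analysis is commonly left to a statistical analysis plan, which is not at hand. On this reply, the point is one inaccurate phrase.

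Much of this stands, and it excludes several stronger readings that a reader might infer.

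- **That the trial's blinding as a whole fails.** The documents do not support this. The research physiotherapists assess the physical outcomes, patients are asked not to tell them their treatment, and neither the visits nor the envelopes contradict that.
- **That concealment is broken.** Those who recruit and enrol are the participating physiotherapists, the research assistant and the research physiotherapist. None is said to see the lists. The envelopes are opaque and sealed, and the principal investigator is said not to select patients. To call concealment guaranteed is strong wording, but no route to selection bias is shown.
- **That the principal investigator knows all 280 allocations.** Possible access to a sequence is not knowledge of who received what.
- **That visiting one arm only is itself a flaw.** The article explains that guideline care is not a protocol. Both arms have training, follow-up meetings and a registration form for each patient. Extra fidelity visits to the standardised arm are a defensible choice.

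The reply does not make the blinding statement true. Nor is this a detail left out of a condensed article: the article asserts the safeguard and also describes the activity that defeats it.

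**Conclusion.** The point holds for the principal investigator only. The stated blinding of this role is incompatible with regular visits to group sessions, and it fails for every intensive-arm patient seen there: 5 to 8 per group visited, with a ceiling of about 140 of 280. The visits decide the matter; the envelopes merely support it.

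This rests on three assumptions: that the common role title denotes one person, that patients attend the treatment allocated, and that those at a session can be recognised as trial participants. Any resulting bias cannot be quantified from the article, and none is shown for the self-reported primary outcomes or the physical measurements. The statement is nevertheless wrong as written about a property that readers use to judge risk of bias, and it should be corrected.

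**What to change.** Choose one of two courses and make the sections agree.

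- **Keep the blinding.** Have the monitoring visits done by the expert trainers already engaged for the intensive arm. The visits are written in the future tense, so this is still open. Have the independent statistician who generated the lists fill any envelopes still to be prepared. The cost is a small reassignment of tasks among people already involved.
- **Keep the visits.** Withdraw the statement that the principal investigator is blinded and leave the statement about the research physiotherapists as it is. Run the effect and cost analyses on coded arms until the analysis decisions are fixed, so that knowledge of allocation cannot influence them. The cost is one less favourable sentence about blinding and the keeping of a code.

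Neither course changes the treatments, the outcomes or the sample size.

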### Interventions

Patients who are assigned to physiotherapy guideline care are treated according to the recently published Low Back Pain Guidelines of the Royal Dutch College for Physiotherapy (KNGF) [9]. The guidelines recommend giving adequate information, advising to stay active and providing exercise therapy with a behavioural approach for patients with sub-acute and chronic low back pain. As the guidelines are relatively new, physiotherapists providing the guideline care receive two training sessions of 2,5 hours each to ensure that the guidelines are properly applied. Preparation time of 2 hours before each session is strongly recommended. Two experts provide background information and discuss the content of the guideline. Video clips and statements on expected barriers are used to start discussions in groups of 10–15 physiotherapists supervised by expert trainers. After 4 months a follow-up session of 2,5 hours is organised to discuss practical problems and to ensure that all physiotherapists are working according to the guideline. The physiotherapists are asked to complete a form for each participating patient they treat, to register treatment goals, content of the treatment, total number of sessions in the treatment period and, if applicable, arguments to deviate from the guideline.

The intensive group training protocol combines exercise therapy with principles of back school and behavioural therapy. Back school principles include group lessons with adequate information on causes of low back pain, factors influencing low back pain, advice on physical activity and dealing with a relapse. Operant conditioning and graded activity as components of behavioural therapy are included in the protocol. Baseline measurements, goal setting and time-contingency are the main elements of the intervention. The purpose of the protocol is to improve activities and participation in work or other social activities, instead of focussing on pain or anatomical impairments. The patient has an active role and is responsible for the results of the therapy. The physiotherapist has the role of coach and focuses on the achieved improvement instead of the remaining complaints [10]. Active behaviour will be reinforced by the physiotherapist.

The protocol has a total duration of 30 weeks and consists of three phases: the starting phase, the treatment phase and the generalisation phase. It concerns 10 individual sessions of 30 minutes per session and 20 group sessions of 1,5 hours per session. During the first phase of three weeks, six individual sessions are planned for patient history and physical examination, providing information on the treatment, determining baseline level of functional capacity and signing a treatment contract. During the treatment phase the group sessions have a frequency of twice a week for eight weeks. Every patient has his own gradually increasing exercise program, with an operant-conditioning behavioural approach based on the baseline level of functional capacity. The treatment phase gradually changes into the generalisation phase in which patients learn to apply everything they have learned in the treatment phase to their own daily situation. Therefore the frequency of the sessions decrease in the last four weeks; patients are encouraged to exercise more at home and to choose a physical activity they will continue after treatment has finished. Two individual sessions are planned for evaluation during the twelve week training period and two additional individual sessions are planned three weeks and three months after the group sessions have finished.

The exercise program consists of:

1. warming-up and cooling down

2. aerobic exercises on a rowing machine, stationary bike or treadmill

3. muscle strengthening exercises of the lower back, abdomen and buttocks

4. exercises that specifically apply to the patient's situation

5. home exercises

The exercises mentioned at point 4. are determined by a Patient Main Complaint Form [11]. During the first intake patients are given this form, consisting of thirty different activities (e.g. turning in bed, lifting, walking, etc.). The patient is asked to select and prioritise the activities he has had trouble with during the last week and would very much like to see improved in the following months. The physiotherapist discusses the form with the patient and designs specific exercises for these activities. Three baseline measurements are performed to determine the maximal performance (for example, the maximum number of repetitions) for each exercise separately. The starting point of the program is 70% of the mean of all three measurements, in order to avoid failure and ensure the experience of success. In agreement with the patient the training quota are determined by the physiotherapist using the starting point, goals and training period to provide a gradually increasing program. The exercise goals are determined by the patient and physiotherapist together to ensure that goals are realistic, concrete, trainable and measurable. The treatment contract is signed by the patient and physiotherapist. The contract states that training quota are always followed exactly and that the patient keeps the graphs of finished sessions.

For training, the physiotherapists will receive instruction on the background and content of the protocol, and will be trained to include behavioural principles in the physiotherapeutic management of low back pain at two meetings of six hours each. In groups of 7–8 physiotherapists discussions and role playing are supervised by one expert trainer with extensive experience in behavioural principles. Four months after the last meeting 2 follow up sessions of 4 hours are organised to discuss practical problems and practice difficult situations with the trainers. The principal investigator ([name]) will regularly visit the group sessions at the physical therapy practices to monitor the conduct of the intensive group training protocol. For each participating patient the physiotherapist is asked to complete a registration form containing the treatment goals, content of the different sessions and evaluation of the protocol.

